The degrees of freedom *v* used in specifying the time function *s*(*t*; *v*) was allowed to vary between 0 (no secular trend) to 8 (4 per year). When the data are generated without a secular trend, all three values for *v* produce consistent estimates of the cook stove effect. However, when in the case where there is a sizeable trend, the *v* = 2,8 models give consistent estimates, but the model that ignores the trend produces strongly biases estimates. The simulation study shows that the design has adequate poser to detect a decrease of 20% or greater relative to baseline (Table 2).

**Table 2 Tab2:** **Power to compare ALRI incidence before and after alternative biomass cookstove installed for varying relative odds and degrees of trend in ALRI rates over time**

	True cook-stove effect (θ)								
	(Relative odds)								
Degree of trend in ALRI incidence	−0.1			−0.2			−0.3		
ν	0	2	8	0	2	8	0	2	8
No trend	88	26	34	100	81	89	100	99	99
Large trend	100	19	37	100	80	87	100	99	99

Based on previous research in this study area, we originally expected approximately 6000 live births in the study area for these trials over 4 years. However fertility declined significantly since that previous research was conducted and a modified expectation was in the range of 3000 live births. Approximately 1% died prior to our being able to weigh them leaving approximately 2350 live births in phase one and 600 in phase two. The mean birthweight in our last trial was 2700 grams with a standard deviation of 437 grams [21]. The intra-sector correlation for birthweight was estimated to be 0.03357. Assuming 80% power and a Type I error of 5% (2- sided), the minimum detectable mean difference in birthweight was approximately 57 g in phase 1 and 83 g in phase two. These detectable differences in mean birthweight are in the range of those reported for infants whose non-smoking mothers are exposed to second hand tobacco smoke during pregnancy and well below the mean differences between women who do and do not smoke during pregnancy.

The rate of low birthweight (<2500 grams) was 29% in our most recent trial in this area and the cluster related design effect for the proportion born low birthweight was 2.36. Assuming a Type I error of 5% (2-sided), a 20% treatment effect, and sample size of 1175 enrolled live births before stove installation and an equivalent number after installation, the power was >80% for phase one but only 47% for phase two.

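### The phase-two birthweight figures (83 g detectable, 47% power for low birthweight) do not follow from 600 births in total, which give about 100 g and about 37%

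*Protocol article*

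**What the plan says.** All the figures are in the Sample size section of the protocol article.

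- **Births.** After a fall in fertility, "a modified expectation was in the range of 3000 live births". Allowing for about 1% who die before weighing, the text arrives at these numbers: "leaving approximately 2350 live births in phase one and 600 in phase two".
- **Mean birthweight.** "The mean birthweight in our last trial was 2700 grams with a standard deviation of 437 grams", and "The intra-sector correlation for birthweight was estimated to be 0.03357". The error rates are given as "Assuming 80% power and a Type I error of 5% (2- sided"), and the detectable difference as "57 g in phase 1 and 83 g in phase two".
- **Low birthweight.** The inputs are a rate of 29%, a 20% treatment effect, two-sided 5% and a cluster design effect of 2.36. Phase one uses a "sample size of 1175 enrolled live births before stove installation and an equivalent number after installation". Power is put above 80% for phase one and at "only 47% for phase two".

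The Design section describes phase two as randomised by household to one of two stoves. The Randomization section adds stratification by VDC and ward. The allocation ratio is not stated.

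**The concern.** With 600 births split between two arms, 83 g is a smaller detectable difference than the stated standard deviation, power and error rate allow. The low-birthweight power is too high in the same direction.

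Birthweight is a primary outcome of both trials. According to the Conclusion, phase two was redesigned because the biomass stove reduced particulates less than expected, so the LPG comparison carries much of the remaining weight. The 83 g figure is used to reassure readers that the detectable differences lie in a plausible range, and it carries no caveat. A null phase-two result read against 83 g and 47% would look more informative than it is.

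**Working it through.** **1. Is 600 a total or a per-arm number?** 2350 + 600 = 2950, close to the 2970 births left when 1% is taken from 3000. The phase-one number is also a two-group total: 1175 + 1175 = 2350. So 600 covers both arms, which means 300 per arm at 1:1.

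**2. Detectable difference in mean birthweight.** Formula: (1.960 + 0.842) × SD × √(2/n per arm).
- n = 300: 2.8016 × 437 × √(2/300) = 99.96 g. Stated: 83 g.
- Power for 83 g at 300 per arm: 64%, not 80%.
- Births needed for 83 g: 2 × (2.8016 × 437/83)² = 435.2, that is 436 per arm.
- Best case, all between-sector variance removed: 99.96 × √(1 − 0.03357) = 98.3 g.

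**3. Power for low birthweight.** 29% versus 0.8 × 29% = 23.2%, pooled-variance test of two proportions, 300 per arm.
- Standard error under the null: √(2 × 0.261 × 0.739/300) = 0.03586. Under the alternative: √((0.29 × 0.71 + 0.232 × 0.768)/300) = 0.03578.
- z = (0.058 − 1.960 × 0.03586)/0.03578 = −0.343, so power is 36.6%. Stated: 47%.
- With continuity correction (0.058 reduced by 1/300): 33.1%.

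**4. Can the stated figures be reproduced?** They can with 600 in *each* arm and a sector design effect of 1 + (m − 1) × 0.03357, where m is births per sector. The Design section gives 51 sectors. The power simulation uses 12 × 4 = 48.

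| Sectors | m = 600/sectors | Design effect | Detectable difference | Low-birthweight power, corrected (uncorrected) |
|---|---|---|---|---|
| 51 | 11.76 | 1.361 | 82.5 g | 47.0% (50.0%) |
| 48 | 12.50 | 1.386 | 83.2 g | 46.2% (49.3%) |

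**5. Other readings at 300 per arm.**
- One-sided 5%: 88.7 g and 48.9%. The power comes near 47%, but the difference does not reach 83 g, and the text says two-sided for both outcomes.
- Design effect of 2.36: low-birthweight power 18.2%.
- Covariate adjustment: it would have to explain 1 − (83/99.96)² = 31% of the variance, and none is stated.
- Unequal allocation moves both figures further away.

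**6. The same check on phase one.** Sector design effects use births per sector per group, and ranges cover 51 to 48 sectors.

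| Births per group | Detectable difference with ICC 0.03357 | Low-birthweight power with design effect 2.36 |
|---|---|---|
| 1175 | 66.6 to 67.5 g | 55% |
| 2350 | 56.6 to 57.7 g | 84% |
| Stated | 57 g | above 80% |

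With no design effect, 1175 per group gives 50.5 g and 89%.

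**The case against.** **The practical consequence is limited.** The trials are described as conducted, and the number of births was set by fertility, not by this calculation. The text already concedes that phase two is weak for low birthweight, and 37% instead of 47% does not change that admission. This stands, and it makes the remedy a correction of reported sensitivity. It does not cover the 83 g figure, which is presented without reservation for a primary outcome.

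**The suggested cause is an inference.** The document does not say how the figures were obtained. The match in step 4 needs all 48 to 51 sectors, although phase two covers two of the four VDCs. With half as many sectors, 600 per arm gives 93.7 to 95.0 g. It also needs the birthweight ICC for the low-birthweight power: the stated design effect of 2.36 with 600 per arm gives 31.8%. The cause therefore remains unproven, but the shortfall at 300 per arm does not depend on it.

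**Stronger readings that the documents do not support:**
- *The two stated figures contradict each other.* They do not. At about 436 to 441 effective births per arm, the difference is 82.5 to 83 g and the continuity-corrected power 46.5 to 47.0%.
- *The birth count is wrong and was really 820 to 870.* Nothing supports such a count, whereas 600 agrees with the stated totals.
- *Clustering makes the result still worse.* Households are randomised within VDC and ward, so both arms occur in the same areas. Geographic correlation does not inflate that comparison and, if modelled, slightly helps.
- *100 g exceeds the 97 g that the Background links to biomass smoke, so phase two could not succeed.* The gap is 3 g, and the Background itself says the underlying observational literature varies in quality. The article's own benchmark, second-hand tobacco smoke, is given without a number.

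**Conclusion.** The phase-two figures are wrong as written. For 600 births in total, the detectable difference is about 100 g instead of 83 g, roughly 20% larger (99.96/83 = 1.20). Low-birthweight power is about 37% instead of 47%. This rests on the stated standard deviation, rates and two-sided 5%, and on 1:1 allocation, which is assumed and is the most favourable ratio. Removing all between-sector variance brings the difference only to about 98 g.

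Use of the total as the per-arm size is the likely explanation, not an established one.

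A reader might infer that phase one is shown to be wrong too. It is not: the stated 57 g lies between the values for 1175 per group without a design effect (50.5 g) and with the ICC (about 67 g), and power above 80% is reached if no design effect is applied. A simple design effect is also only a rough stand-in for a stepped-wedge comparison. The pattern in step 6 is a reason to recheck.

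**What to change.** In the Sample size section, restate phase two as a detectable difference of about 100 g and low-birthweight power of about 37%, for 600 births in total (about 300 per arm). State the allocation ratio, and apply no sector design effect to this household-randomised comparison. Keep the 600.

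Recheck the phase-one figures of 57 g and above 80% with 1175 per group, and state which clustering allowance was used.

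The cost is one paragraph of text and a short recalculation. Recruitment, data collection and analysis are unaffected.

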**Trials design scheme.**

This standard step-wedge design was modified by adding a six month period of outcome assessment in all groups prior to the start of the step-wedge and a similar six month period of outcome assessment following completion of the 12 month step wedge. This provided additional person-time and balance on season both before and after new stove installation. All three primary outcomes show marked seasonality in this population [15, 16].

Phase Two: The design of phase two was an individually randomized trial at the household level (Figure 1). Eligible households that participated in phase one and newly eligible households that did not participate in phase one were randomized to either an alternate biomass stove with chimney or a LPG stove with gas tank and 12 month supply. Follow-up of phase two was for 12 months following stove installation.

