### Health effects modeling

To estimate the effect on ALRI of having a new cook stove installed in the home, while fully accounting for the salient features of the stepped wedge trial design [20] and for sources of variation at both the individual and village levels, we used a generalized mixed effects model as summarized in Hussey and Hughes [20]. Let *Y*_*ijt*_ denote a positive ALRI response for individual *j* = 1,…,*N* from village *i* = 1,…,*I* at time point *t* = 1,…,*T*. Let *p*_*ijt*_ denote the risk of ALRI, that is the expected value for *Y*_*ijt*_. We assume *p*_*ijt*_ satisfies the logistic random effects model:
1

where: *α*_0_ is the overall baseline log odds of having ALRI;  is the random effect for cluster *i* to account for correlation among children from the same village*;* is the random effect for child j in cluster *i* to account for possible within-child-level correlation; *s*(*t*, *v*) is a fixed, smooth function of time to control for secular and seasonal trends; and *θ* is the fixed cook stove intervention effect that is of primary scientific interest. In this model, we will represent *s*(*t*, *v*) by natural cubic splines with *v* degrees of freedom. A priori, with two years of data, we chose *v* = 8 (4 degrees of freedom per year) but will conduct sensitivity analyses to determine whether the major findings are sensitive to this choice over a range of reasonable choices *v* = 4 to 12 for this smoothness constraint. The generalized linear mixed model above will be estimated using the method of maximum likelihood as implemented in the R package *glmer (*http://cran.r-project.org/web/packages/lme4/lme4.pdf*)*. Robust variance estimates of the stove effect coefficient will be calculated and compared to the model based values as a sensitivity analysis to check on the assumed correlation model within children and among children within villages. If the robust variances are significantly larger than their model-based counterparts, the former will be used for testing and confidence interval calculations.

A similar approach will be used to estimate the treatment effect on birthweight. While seasonality of birthweight and other reproductive outcomes is present in this population, it is not as dramatic as seen for ALRI, nor is the clustering by sector as high [16]. Birthweight will be treated as both a continuous variable and as dichotomous with low birthweight defined as weights <2500 g.

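### The birthweight power calculation and single-effect model ignore pregnancies under way at installation; a yes/no stove indicator with the planned time spline would recover about 0.22 of an evenly building whole-pregnancy effect

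*Protocol article*

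**What the plan says.** Under Sample size, the article expects births "leaving approximately 2350 live births in phase one and 600 in phase two". For low birthweight in phase one it assumes a "sample size of 1175 enrolled live births before stove installation and an equivalent number after installation". Since 2 × 1175 = 2350, every phase one birth falls on one side or the other. The stated detectable differences in mean birthweight are 57 g (phase one) and 83 g (phase two). They are justified by comparison with second-hand and active smoking during pregnancy.

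Health effects modeling describes the ALRI model: one fixed stove effect, random effects for cluster and child, and a natural cubic spline in time with 8 degrees of freedom, varied from 4 to 12 in sensitivity analyses. It then says: "A similar approach will be used to estimate the treatment effect on birthweight". No lag, trimester, duration or exclusion rule is given for pregnancies under way at installation.

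The phase one calendar is six months before any installation, twelve monthly steps and six months afterwards. For the second trial: "Follow-up of phase two was for 12 months following stove installation". The LMP date is recorded at pregnancy enrollment.

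**The concern.** An ALRI episode can respond to a stove soon after it is installed. Birthweight reflects exposure over a gestation. A birth six weeks after installation had the old stove for most of the pregnancy, yet the power calculation gives it the same weight as a birth conceived after installation, and a single on/off stove term would do the same.

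The time-adjusted stepped-wedge estimator makes this worse. Once a spline absorbs calendar time, the stove coefficient rests largely on months in which some sectors have just switched and others have not. That is when exposed gestation is shortest. Sectors that switched earlier, whose births are more fully exposed, also serve as comparators for newly switched ones. Birthweight is a primary outcome, so a real benefit could be reported as little or nothing.

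**Working it through.** **Inputs.** From the article: 51 sectors, 12 groups, the 6 + 12 + 6 month calendar, 2350 births in phase one and 600 in phase two, SD 437 g, ICC 0.03357, two-sided 5%, 80% power, spline df 8 (range 4 to 12). The 97 g observational association is in Background. Assumed: births uniform in time and nine months' gestation. Using 40 weeks (9.2 months) instead changes the mean exposed share only from 0.628 to 0.621.

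**The stated 57 g.** MDD = (1.96 + 0.8416) × 437 × √(2 × DEFF / n).
- n = 1175, no clustering: 50.5 g.
- n = 1175, DEFF = 1 + (23.04 − 1) × 0.03357 = 1.740 (1175/51 births per sector): 66.6 g.
- n = 1175, DEFF = 1 + (46.08 − 1) × 0.03357 = 2.513 (2350/51 births per sector): 80.1 g.
- n = 2350 in each group, DEFF 2.513: 56.6 g.

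So 57 g is matched only if the total is used as the group size. That is a separate matter. What counts here is that no version contains a term for exposed gestation.

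**Exposure of births after installation, phase one.** With mid-month installation, group follow-up L after installation runs from 6.5 to 17.5 months and sums to 144 group-months, with 144 before. This matches the 1175:1175 split.
- Fully exposed: Σ max(L − 9, 0) = 40.5, and 40.5/144 = 28%. Start-of-month installation gives 45/150 = 30%. If the three sectors beyond 12 × 4 = 48 also fall in the earliest groups, it is 204/651 = 31%.
- Mean share, even build-up: L − 4.5 for the nine groups with L ≥ 9 sums to 81; L²/18 for the other three sums to 9.49; 90.49/144 = 0.63.
- Last three months only: (144 − 12 × 1.5)/144 = 0.875.
- First three months only: (54 + 1.46)/144 = 0.385.

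**What the time-adjusted model returns.** The expected generalised least squares coefficient is (ΣX′V⁻¹X)⁻¹ ΣX′V⁻¹μ. Here μ is the true exposed share, sector variance is 437² × 0.03357 = 6411, residual variance is 437² × 0.96643 = 184,558, and there are 2350/(51 × 24) = 1.92 births per sector-month. X holds the spline (v = 8) and the exposure term. Power is for a 97 g whole-pregnancy effect.

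| True window | Yes/no, no time terms | Yes/no, v = 8 | Power | Share of gestation, v = 8 | Power |
|---|---|---|---|---|---|
| Even over 9 months | 0.63 | 0.22 | 10% | 1.00 | 46% |
| Last 3 months | 0.88 | 0.63 | 45% | 0.90 | 39% |
| First 3 months | 0.39 | −0.11 | 6% | 0.90 | 39% |

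Standard errors at v = 8 are 33.2 g (yes/no) and 52.2 g (share). With v = 4 or 12 the yes/no coefficients stay at 0.22, 0.63 and −0.10 to −0.11, so the planned sensitivity analysis would not reveal the problem.

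**Detectable differences, time-adjusted.** Yes/no: 2.8016 × 33.2 = 93 g. Share: 2.8016 × 52.2 = 146 g per full gestation. The gap from 57 g therefore has two sources: time adjustment (57 to 93 g) and expressing the effect per full gestation (93 to 146 g).

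**Phase two.** With births uniform over 12 months, the mean share is (12 − 4.5)/12 = 0.625 and 3/12 = 25% are fully exposed. Under even build-up, the stated 83 g corresponds to 83/0.625 = 133 g per full gestation.

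**The case against.** **The coding is inferred.** The before/after split is a power assumption, not a definition of how births enter the analysis. The model equation was not readable in the copy used here, and the birthweight sentence is one line. An analysis plan not shown may define exposure differently. This stands as a limit on certainty. But a single stove effect carried over to birthweight, with every birth assigned to before or after, leads a literal reader to a yes/no term.

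**The effect of installation is a legitimate target.** The average effect on births in the study period needs no full-gestation scaling, and the test stays valid under the null. That defends a crude before/after mean, which does return the average share (0.63 under even build-up). It does not defend the time-adjusted coefficient: 0.22 is neither 1 nor 0.63. Dropping the time terms is no escape, because the article's own simulations show strong bias when a trend is ignored.

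**The size depends on an unknown window.** It does, so three windows are shown. None returns the average effect among births after installation.

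**Stronger readings that the article does not support.**
- A reader might infer that pregnancies exposed for only days drive the loss. Births within a week of installation are about 2% of those after it, and within a month about 8%. Most of the loss comes from births with one to nine months of exposure.
- A reader might compute lower recoveries, near 0.15 (even) and 0.51 (last three months). These arise only if installation is mid-month but the whole month is coded as treated. Conversely, a coarse monthly grid that drops the installation month gives about 0.25 and 0.72.
- A reader might expect share coding to give about 70% power for 97 g in the late-window case. That needs a last-three-months variable, which presupposes the window.
- A reader might apply 97 g to phase two. That trial compares LPG with an improved biomass stove, which is not the contrast behind the 97 g.

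**Conclusion.** The point holds for phase one as a strong inference from the text, not as an explicit definition in it. The birthweight power calculation makes no allowance for partial gestational exposure, and the model as described has no term for it. Under a nine-month gestation, uniform births and the article's ICC and SD, a yes/no indicator with the planned spline recovers about 0.22, 0.63 or −0.1 of a whole-pregnancy effect, depending on the window. It estimates neither the full-gestation effect nor the average effect among births after installation. The stated 57 g should not be read as a full-gestation detectable difference; for the time-adjusted model that is about 146 g.

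For phase two the conclusion is narrower. The 83 g refers to births with a mean exposed share of about 0.625. No phase two birthweight model is stated, so no further claim is made about its estimator.

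**What to change.** **Phase one.** Define the birthweight exposure variable as the share of the 40 weeks from LMP that falls after the sector's randomised installation month. Report the effect per full gestation and keep the yes/no indicator as a sensitivity analysis. A fixed 40-week window keeps the variable independent of gestational length, which is itself a primary outcome. Restate the detectable difference as about 146 g per full gestation for the time-adjusted model.

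**Phase two.** State that 83 g refers to partly exposed births, and add a supporting analysis of births conceived after installation (about 25%).

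**Cost.** Only analysis wording changes: LMP dates are collected and the installation months were randomised. The downsides should be stated. The standard error rises from about 33 g to 52 g. Power for 97 g rises from about 10% to 46% under even build-up, but falls slightly, from about 45% to 39%, if only the last three months matter. Share coding is also not exact when the true window is narrow: it recovers about 90% of the effect in the two three-month cases.

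### The phase-one low-birthweight power of more than 80% follows neither from the design effect of 2.36 given beside it nor from the planned calendar-time-adjusted model

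*Protocol article*

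**What the plan says.** All the inputs stand in the last two paragraphs of the protocol article's Sample size section.

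- Baseline: "The rate of low birthweight (<2500 grams) was 29% in our most recent trial in this area".
- Clustering: "the cluster related design effect for the proportion born low birthweight was 2.36".
- Error rate and effect: "Assuming a Type I error of 5% (2-sided), a 20% treatment effect".
- Numbers: "sample size of 1175 enrolled live births before stove installation and an equivalent number after installation". These come from the split "leaving approximately 2350 live births in phase one and 600 in phase two".
- Conclusion: "the power was >80% for phase one but only 47% for phase two".

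The text does not say that 2.36 was set aside, reduced or replaced for phase one.

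The Health effects modeling section specifies the analysis for acute lower respiratory infection (ALRI): a stepped-wedge mixed model with random effects for village and child and a smooth function of calendar time, with 8 degrees of freedom chosen in advance. It then says that birthweight will be handled in a similar way, both as a continuous variable and cut at 2500 g.

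**The concern.** A design effect of 2.36 cuts the information in a parallel-cluster comparison to well under half. A reader who sees it quoted just before the power statement will assume that the power allows for it. The inputs give more than 80% only if the factor used is much smaller than 2.36 and calendar time is left out of the model.

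What is at stake is how a null result is read. The Conclusion section already reports that the stove reduced particulate concentrations less than anticipated, so a null phase-one result is a realistic prospect. If phase one is described as having more than 80% power for a 20% reduction, in contrast to a phase two with 47%, a null result will be taken as fair evidence against an effect of that size. On the planned analysis, the chance of detecting it is below one half.

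**Working it through.** **Inputs.** From the Sample size section: p1 = 0.29; a 20% relative reduction, so p2 = 0.8 × 0.29 = 0.232; difference 0.058; n = 1175 per period; two-sided 5%. The relative reading is the right one: a 20-point absolute drop (29% to 9%) would put power near 100% in both phases, which the stated 47% for phase two rules out.

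**Step 1: the plan's own figure.** Two proportions, pooled variance under the null:

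power = Φ{ [ |p1 − p2| √n − 1.96 √(2 p̄(1 − p̄)) ] / √( p1(1 − p1) + p2(1 − p2) ) }

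with p̄ = 0.261, √(2 × 0.261 × 0.739) = 0.621 and √(0.2059 + 0.1782) = 0.620.

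At n = 1175: (1.988 − 1.217)/0.620 = 1.24, so power is 89.3%. The stated figure reproduces with no design effect.

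**Step 2: 2.36 in full.** Effective n = 1175/2.36 = 498 per period. Then (1.294 − 1.217)/0.620 = 0.124, so power is 54.9%. Unpooled, arcsine and continuity-corrected versions give 52–55%. At this effective n, 80% power needs a relative reduction of about 27% (78.3% at 26%, 81.4% at 27%).

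**Step 3: the largest factor compatible with 80%.** The same formula needs 899 effective births per period for 80% power, and 1175/899 = 1.31.

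**Step 4: was a smaller factor used?** The same section gives a phase-one detectable birthweight difference of about 57 g, with a standard deviation of 437 g. Without clustering the figure is 2.80 × 437 × √(2/1175) = 50.5 g. The implied factor is (57/50.5)² ≈ 1.27. Applied to low birthweight, 1.27 gives an effective n of 925 and power of 81%. The article states no such factor for either outcome.

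**Step 5: the planned type of model.** A linear generalised least squares calculation for a stepped wedge with 6 months before, 12 monthly steps and 6 months after. The variance of the stove effect is the first diagonal element of (Σ X′V⁻¹X)⁻¹, summed over sectors. X holds the stove indicator and the time terms. V is the within-sector covariance of monthly proportions, with total variance 0.261 × 0.739 = 0.193 and an exchangeable intra-sector correlation. Power = Φ(0.058/SE − 1.96). Assumptions: 2350 births spread evenly over 24 months; 51 sectors (Design section) or 48 (4 in each of 12 groups, as in the ALRI power assumptions); correlation 0 to 0.06; installation month counted as half or fully exposed.

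| Time adjustment | SE | Power |
|---|---|---|
| None | 0.018–0.019 | 87–89% |
| 8-df spline or monthly effects | 0.031–0.037 | 35–46% |

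At the ends of the adjusted range: 0.058/0.0312 − 1.96 = −0.10 gives 46% (51 sectors, correlation 0, month fully exposed); 0.058/0.0366 − 1.96 = −0.38 gives 35% (48 sectors, correlation 0.06, month half exposed). Under the same model, 80% power is reached at a relative reduction of about 30–35%.

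**Step 6: the article's own evidence for this cost.** In Table 2, at a stove effect of −0.1 with no trend, ALRI power falls from 88 with no time term to 26 with 2 degrees of freedom and 34 with 8.

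**The case against.** The strongest defence is that 2.36 does not belong in a phase-one calculation. Sectors contribute births both before and after installation, so sector effects largely cancel. Step 5 supports this: without a time term, power is 87–89%. Nor is 2.36 clearly transferable, because a design effect depends on cluster size. If the continuous-birthweight value ("The intra-sector correlation for birthweight was estimated to be 0.03357") is borrowed for the binary outcome, 2.36 implies about 41 births per cluster (1.36/0.03357 ≈ 40.5, plus 1), whereas phase one has about 2350/51/2 = 23 per sector per period. Even as parallel clusters that gives 1 + 22 × 0.03357 = 1.74 and 68% power. All of this stands, so 55% should not be read as the true phase-one power.

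The defence does not restore more than 80%, because it needs an analysis with no time term. The Sample size section itself warns that ignoring a sizeable trend gives strongly biased estimates. It is true that birthweight is described as less seasonal than ALRI and that the 8 degrees of freedom are set for ALRI. But a 3-df time curve still gives only about 40–50%.

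A reader might also infer that clustering was simply forgotten. The documents do not show that: the 57 g figure is compatible with a factor near 1.27, which would give 81%. They show only that 2.36 was not applied in full and that no replacement is stated.

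Finally, the listed primary outcome is birthweight. The under-2500 g form is an additional analysis of it, and continuous birthweight has its own detectable difference. The point limits what can be claimed for low birthweight; it does not show that the trial or its primary outcome fails.

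**Conclusion.** The point holds as a misstatement of power. More than 80% for phase one requires an unstated design effect of at most about 1.31 and no adjustment for calendar time. The factor printed beside it gives 55%, and the planned type of model gives about 35–46%.

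The 89%, 55% and 1.31 follow from the article's inputs alone. The 35–46% range rests on the assumptions in Step 5, including an intra-sector correlation for the low-birthweight proportion that the article does not give, and on reading the similar approach for birthweight as including a calendar-time term. The conclusion that power is well below 80% holds across all the time-adjusted settings tried; the exact figure does not.

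**What to change.** In the Sample size section, replace the phase-one statement with the power under the planned time-adjusted model, about 35–46% for a 20% relative reduction, and list its assumptions (number of sectors, spread of births, intra-sector correlation, time terms, handling of the installation month). Give about 30–35% as the relative reduction detectable with 80% power under that model.

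If the simple two-proportion calculation is kept, report it separately as 55% with 2.36, with 80% power at about a 27% reduction. The 27% must not be attached to the time-adjusted model. Alternatively, state and justify the smaller factor that was used.

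No more births and no change of design or analysis are needed. The only cost is a less favourable stated power.
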